2. Is it possible to explain the recovery of dexterity in the paretic extremity during the first 6 months post stroke from the changes in cortical activation found in the first 4 weeks on fMRI in M1, vPMA, dPMA and SMA cortices of infarcted and non-infarcted cerebral hemispheres in patients with primary ischemic middle cerebral artery stroke?
3. Are changes in fMRI patterns in the contra-lesional cortex (M1) related to the impact of cortico-spinal tract degeneration as established with TMS within the first week and at 6 months post stroke?
4. What is the predictive value of TMS parameters such as motor threshold, motor evoked potential (MEP) and the subsequent ‘silent period’ (cortical inhibition phenomenon) for functional outcome at 6 months?
5. Which muscles of the paretic limb (i.e., intrinsic hand muscles, finger and wrist extensors or upper arm muscles) are most sensitive and specific in predicting functional outcome at 6 months post stroke?

Project B2: kinematics

*Research questions:*

1. Can functional improvement of the paretic arm during the first 6 months be explained by behavioural strategies to compensate for deficits (e.g., bending and rotating the trunk) in a standardized reaching task?
2. What is the relation between kinematic changes observed during functional recovery and dynamic changes in cerebral motor networks?

Project B3: haptic robot

*Research questions*

1. How and to what extent do endpoint mechanical behaviour (at the wrist joint) and peripheral reflex chain properties change during follow-up after stroke?
2. Does CIMT or EMG-NMS affect endpoint mechanics and peripheral reflex chain properties?
3. How do endpoint mechanics relate to upper limb performance in executing a reaching task?
4. How are these parameters and changes in parameters in the course of time influenced by CMIT or EMG-NMS?

*2.3 Project C: longitudinal relations. Objective: analysing the longitudinal relations between the results of project B.*

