Relatively poor recovery profiles in terms of neurological deficits (FM-score, MI-arm score, somatosensory deficits and neglect) and ARAT may be associated with: 1) the use of compensation strategies (expressed as bending and rotating the trunk towards an object) and 2) the amount of contra-lesional activation in fMRI and TMS (i.e., recruitment of cerebral activity). Those patients showing a normalization of ARAT outcome (i.e. > 53 points) are expected to show: 1) normalization of kinematics and 2) focusing of cortical activity on the original physiological areas involved (i.e. M1, SMA, CC dPMA and vPMA) and intactness of corticospinal tract on TMS.

*Research question*:

How are improvements in dexterity longitudinally related to observed changes in neurological impairments, kinematics and biomechanics and to changes in cortical activation patterns as revealed by fMRI and TMS?

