###### Additional clinical assessment in Project B

- fMRI week 2, 5 en 26
- TMS week 2, 5 en 26 ( MEP in week 1)
- Haptic robot week 1,2,3,4,5,8,12,26
- Kinematics week 2,3,4,8,26

See also appendix 2

*4.7 Burden and risks*

We are aware of the burden on patients of early intervention and clinical measurements in their early stage of recovery. However, evidence is compelling that in the first weeks after stroke functional outcome is determined. If the treatment has to have any effect on primary outcome it should be applied in the early phase after stroke. Next to the opportunity to evaluate early applied intensive therapy we expect to find answers to fundamental research questions that are vital to our understanding of functional recovery after paresis of the upper limb, which is a prerequisite for future optimal treatment planning.

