To investigate the possible longitudinal association between recovery of dexterity on ARAT and covariates, bi-variate longitudinal regression analysis will initially be conducted, including ARAT change scores (i.e. first-order regression) and time-independent covariates at baseline, such as age, gender and lateralization of stroke, as well as change scores of the time-dependent covariates: MI-arm, FM-arm (including wrist), FM-hand, letter-cancellation task and Active Range of Motion (RoM) of trunk rotation and trunk bending during reaching. (Kollen et al, 2005; Kwakkel et al, 2006) Treatment intervention will be used as one of the covariates in the quasi-causal regression model. (Kwakkel, 1999.) Subsequently, standardized regression coefficients will be calculated and a multivariate, first-order regression model to predict functional change on ARAT will be developed. The -2log likelihood ratio test will be calculated to evaluate the necessity of allowing random regression coefficients into the model, and the Wald test will be used to obtain a P value for a particular regression coefficient. A two-tailed significance level of .05 will be used for all tests.

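### Section 5.3's longitudinal model leaves out the fMRI, TMS and haptic measures that Project C asks about, and it states no time term

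*Protocol*

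**What the plan says.** Protocol section 2.3 gives Project C's objective as "analysing the longitudinal relations between the results of project B". Its research question links improvement in dexterity to neurological impairments, "kinematics and biomechanics and to changes in cortical activation patterns as revealed by fMRI and TMS".

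Section 5.3 gives the analysis. ARAT change scores are regressed on "time-independent covariates at baseline, such as age, gender and lateralization of stroke" and on "change scores of the time-dependent covariates: MI-arm, FM-arm (including wrist), FM-hand, letter-cancellation task and Active Range of Motion (RoM"), the last item referring to trunk rotation and trunk bending during reaching. Treatment is a further covariate. A likelihood-ratio test decides on random coefficients, and Wald tests give the P values.

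Section 4.6 sets the Project B visits: "fMRI week 2, 5 en 26", TMS in the same weeks with an additional MEP in week 1, and "Kinematics week 2,3,4,8,26". The haptic robot and the ARAT are both scheduled at weeks 1, 2, 3, 4, 5, 8, 12 and 26.

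Two Project B questions in section 2.2 depend on this schedule. B2 question 2 asks "What is the relation between kinematic changes observed during functional recovery and dynamic changes in cerebral motor networks". B1 question 2 seeks to explain recovery from "changes in cortical activation found in the first 4 weeks on fMRI".

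**The concern.** Section 5.3 is the only place where a longitudinal model for Project C is written down. If it is run as written, the cortical, corticospinal and biomechanical parts of the question get no estimate from it, although those data are collected for this purpose.

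The associations that are estimated carry a second problem. Recovery after stroke is fast early and slow later, and the visits are unevenly spaced. A regression of change on change that pools intervals without a time term can pick up the common recovery curve and present it as a link between two measures.

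The timetable adds a smaller difficulty. Kinematics is the one Project B series not measured at week 5, when the second fMRI and TMS sessions take place. That limits how exactly changes in movement strategy can be matched to changes in cortical activation.

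**Working it through.** The protocol gives no sample size or power figure for Project C, so there is none to reproduce. The check compares the question with the model and then the visit lists with each other.

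**1. Question (section 2.3) against time-dependent covariates (section 5.3)**

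| Part of the question | In the model? |
|---|---|
| Neurological impairments | Yes: MI-arm, FM-arm, FM-hand, letter cancellation |
| Kinematics | Yes: trunk rotation, trunk bending |
| Biomechanics (haptic robot) | No |
| Cortical activation (fMRI) | No |
| TMS | No |

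The open-ended wording in 5.3 applies to the baseline covariates only. The time-dependent covariates follow a colon as a complete list. Elsewhere in section 5, the subsection on Project B contains only sample-size calculations for B1 and B3. The opening paragraph announces correlation and regression of the outcome variables in general terms, without a longitudinal model.

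**2. Interval lengths (section 4.6)**

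- ARAT at weeks 1, 2, 3, 4, 5, 8, 12, 26: gaps of 1, 1, 1, 1, 3, 4 and 14 weeks.
- Kinematics at weeks 2, 3, 4, 8, 26: gaps of 1, 1, 4 and 18 weeks.
- fMRI and TMS at weeks 2, 5, 26: gaps of 3 and 21 weeks.

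**3. Why a time term matters**

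Write two measures as mean curve plus patient deviation, Y = f(t) + u and X = g(t) + v, with u and v unrelated. Over interval k, ΔY = Δf_k + Δu and ΔX = Δg_k + Δv. Pooled over intervals with no time term, the slope of ΔY on ΔX tends to

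Cov_k(Δf_k, Δg_k) / [Var_k(Δg_k) + Var(Δv)].

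If both curves have the same shape, Δf_k = c·Δg_k with c > 0. The numerator is then c·Var_k(Δg_k), which is positive whenever mean gains differ between intervals, even though u and v are unrelated. With interval indicators, Δf_k and Δg_k are absorbed and the numerator becomes Cov(Δu, Δv) = 0. The bias therefore depends on how much mean gains vary across intervals relative to within-patient variation. The protocol gives neither quantity for these measures.

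**4. Overlap of visits**

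- fMRI/TMS {2, 5, 26} ∩ kinematics {2, 3, 4, 8, 26} = {2, 26}.
- Consecutive intervals are 2–5 and 5–26 for fMRI/TMS, and 2–3, 3–4, 4–8 and 8–26 for kinematics. None coincides.
- One exactly matched change per patient remains: week 2 to week 26, that is 26 − 2 = 24 weeks.
- With kinematics at week 5, the shared visits would be 2, 5 and 26, giving two matched changes (2–5 and 5–26).
- ARAT and haptics are measured at weeks 2, 5 and 26, so their changes can already be matched to both fMRI/TMS intervals.

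**5. B1 question 2**

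Of the scans at weeks 2, 5 and 26, only the first carries a week label of 4 or less. Whether the week-5 scan closes the four-week window depends on how weeks are counted, which the text does not settle.

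**The case against.** The strongest reply is that the model in 5.3 already addresses the programme's central contrast. The protocol treats trunk bending and rotation as the marker of compensation, and FM-arm reflects impairment. Both are in the model. This stands: a reader might infer that repair versus compensation is not analysed at all, and the protocol does not support that. The gap is confined to the fMRI, TMS and haptic measures.

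A second reply is that the general sentence opening section 5 points to section 3, where the Project B measures are listed, so some regression on them is planned. That is fair, but the sentence gives no longitudinal specification and so does not supply what 5.3 lacks.

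A third reply is that a time term can be left to a statistical analysis plan, and 5.3 does not rule one out. This has weight and makes the time term the softer part of the point. Still, 5.3 specifies the outcome, covariates, treatment term, random coefficients and tests, and a reader following it would fit no time term.

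A fourth reply is that staggered sessions do not prevent a joint analysis. Kinematics from week 2 to week 4 falls one week short of the week 2 to week 5 scan interval, and a longitudinal model can use nearby visits. This also stands. A reader might infer that the timetable blocks the analysis or leaves the early scan change with no kinematic counterpart, but only exact matching is lost. Moving the week-4 session would also have a price, since therapy is scheduled for weeks 1 to 4 and that session is the last kinematic measurement within it. Section 4.6 also refers to an appendix that is not available here.

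**Conclusion.** The point holds in limited form. Section 5.3 does not match Project C's own question: impairments and trunk kinematics are in the longitudinal model, and fMRI, TMS and haptic measures are not. This follows from the text alone.

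The missing time term is a real weakness of the stated change-score model, given intervals of 1 to 14 weeks (ARAT) and 1 to 18 weeks (kinematics). The argument assumes that the measures share a decelerating mean recovery. The direction is towards apparent association between unrelated measures. A reader might want an inflated error rate attached to this, but any such figure would rest on a recovery curve and noise levels that the protocol does not give.

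The week-5 mismatch is secondary. Under exact matching, B2 question 2 has one change per patient instead of two. The window in B1 question 2 is a wording matter. Neither ARAT trial in Project A is affected.

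**What to change.** In section 5.3, for the Project B subset, add the following as time-dependent covariates at the visits where they are measured:

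- change in fMRI activation (ipsilesional and contralesional regions);
- change in TMS response (MEP);
- change in haptic reflex gain.

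Add time since stroke, or interval indicators, to every change-score model.

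For kinematics, choose one of two courses and state it. Either align a session with week 5, accepting the loss of an in-therapy point if an existing session is moved, or declare that week-4 kinematics is paired with week-5 fMRI and TMS. Reconcile the window in B1 question 2 with the week-2 and week-5 scans.

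The cost is mainly wording, since the missing measures are already collected. The fMRI and TMS models will have few data: at most two consecutive changes per patient in up to 30 + 30 = 60 patients, and fewer for fMRI because of its wrist and finger extension requirement. Interval indicators use a few degrees of freedom.

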# Summary

Prospective cohort studies show that about 80% of all stroke survivors have an upper limb paresis immediately after stroke. Only one third of all stroke patients will regain some dexterity, whereas well-researched evidence based therapies for an effective treatment of the upper limb are lacking.

However, the main claim of the literature is that functional recovery of the upper paretic limb is mainly defined within the first month post stroke and that rehabilitation services should be applied preferably within this time window of recovery. Furthermore, it is known that exercise-related interventions are most effective when they are applied intensively in a task-oriented way. The program EXplaining PLastICITy after stroke (acronym: EXPLICIT-Stroke) builds on the existing knowledge about functional prognosis and effectiveness of exercise therapy in patients with a first-ever MCA stroke.

The two RCT’s of EXPLICIT are aimed to investigate the effects of early intensive intervention, i.e. 1) early applied Constraint Induced Movement Therapy (CIMT) in patients with a known favourable prognosis for functional recovery and 2) early started sensorimotor stimulation program by Electromyography-triggered neuromuscular electrical stimulation (EMG-NMS) in patients with a poor probability for functional recovery of the upper limb. In both single-blinded RCT's, interventions will be compared to usual practice (standard rehabilitation program).

To improve our knowledge on what patients learn when they show functional recovery, EXPLICIT will explore the underlying mechanisms that are involved in regaining dexterity. For this latter purpose, a longitudinal study is performed on the impact of intactness of the primary motor system as revealed with TMS to be related to: 1) changes in cortical activation patterns of ipsi- and contralateral brain by fMRI; 2) adaptive motor control of the upper limb (kinematics) and 3) changed stiffness of the upper paretic limb by haptic robotics in a repeated measurement design.

By this, EXPLICIT will provide an answer to the key question whether therapy induced improvements are due to either a reduction of basic motor impairment by neural repair (i.e., restitution of function) and/or the use of behavioral compensation strategies (i.e. substitution of function).

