A few studies have found that improvements induced by CIMT (Dijkhuizen et al, 2001; Schaechter et al, 2003) or EMG-NMS of the affected upper limb (Stephan et al, 1997; Kimberley et al, 2004) coincide with cortical reorganizations of motor maps in patients suffering from chronic stroke. This suggests that neuroplasticity is an important mechanism for functional recovery of the upper paretic limb. However, the impact of the above-mentioned therapies on dynamics of cortical reorganization has never been investigated in patients with (sub)acute stroke.

Recent longitudinal studies also suggest that functional recovery is more than neural repair alone. Repeated measurements in time show that improved reaching and grasping activities with the paretic upper limb depends also on adaptive trunk movements (Cirstea et al, 2003; Kwakkel et al, 2004b).

Therefore, understanding functional recovery of the upper limb requires not only knowledge about longitudinal changes in neuroplasticity but also knowledge about the compensation strategies patients use and the changing biomechanics in motor control as a function of time

The functional impact of the time-dependent changes in cortical neuroplasticity, as well as the adaptive compensation strategies used to deal with existing motor deficits and biomechanical constraints, need to be explored in order to improve our knowledge about what exactly patients learn when functional improvement is observed.

This study aims to get a better understanding of the neurobiological background of functional recovery of the upper limb after stroke, especially focussing on early intervention.

The results of EXPLICIT will allow clinicians to define both the optimal treatment strategy and its time window in rehabilitation in the near future.

The clinical outcome measures may serve as a template for understanding functional recovery by elucidating the longitudinal relationship between the body functions, body structures, activities and participation (as described in the International Classification of Functioning (ICF). The EXPLICIT-study is designed to answer the following questions: Is early intervention with CIMT or EMG-NMS effective compared to our current rehabilitation programme? How are therapy-induced improvements in upper limb function after stroke longitudinally related with observed changes in (sub)cortical reorganisation and using compensation strategies?

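### The Project C model suits its own question about recovery in general, but it cannot by itself answer the programme's key question about therapy-induced improvement, and no arm contrast is stated for trunk movement

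*Protocol*

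**What the plan says.** **Programme question.** The Summary says the programme will answer the "key question whether therapy induced improvements are due to either a reduction of basic motor impairment by neural repair" or to behavioural compensation, or both. Section 1 repeats the idea as a study question: "How are therapy-induced improvements in upper limb function after stroke longitudinally related with observed changes in (sub)cortical reorganisation and using compensation strategies".

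**Project C question.** Section 2.3 asks something narrower: "How are improvements in dexterity longitudinally related to observed changes in neurological impairments, kinematics and biomechanics", and also changes in cortical activation. It does not restrict this to improvement caused by therapy.

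**Model.** In section 5.3 the outcome is ARAT change. The covariates are baseline characteristics "as well as change scores of the time-dependent covariates: MI-arm, FM-arm (including wrist), FM-hand, letter-cancellation task" and trunk rotation and bending during reaching. On treatment the section says: "Treatment intervention will be used as one of the covariates in the quasi-causal regression model". Bivariate regressions come first, then "a multivariate, first-order regression model to predict functional change on ARAT will be developed", and "the Wald test will be used to obtain a P value for a particular regression coefficient", two-tailed at 0.05. Section 5.3 states no effect of treatment on the change scores, no treatment-by-covariate term and no indirect effect.

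**The concern.** Whether therapy-induced gain comes from repair or from compensation is a causal question about the randomised arms. It needs to be known whether therapy changed the candidate route, and whether that change accounts for the ARAT gain. The model in section 5.3 addresses neither.

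- A significant FM-arm or trunk coefficient says that patients who change more on that measure also change more on ARAT. Patients who recover spontaneously will show this in either arm.
- The treatment coefficient holds FM-arm and trunk change fixed. These are measured after randomisation and are the routes through which therapy is supposed to act. The coefficient is the remaining effect outside those routes, not the total effect of therapy.

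At stake is the programme's headline mechanistic statement. The primary comparisons in A1 and A2 are not affected.

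**Working it through.** Section 5.3 gives no sample size or power figure for Project C, so there is no figure to reproduce. The check is structural, with an illustration.

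**1. What the model estimates.** Let Z be the randomised arm, F the change in FM-arm, T the change in trunk movement and Y the change in ARAT.

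- Effects of therapy on the routes: F = aF·Z + noise; T = aT·Z + noise.
- Section 5.3 model, in its simplest reading: Y = c·Z + bF·F + bT·T + noise.
- Total effect of therapy on ARAT: c + aF·bF + aT·bT.

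The key question concerns aF·bF (repair) and aT·bT (compensation). The model returns c, bF and bT. It contains neither aF nor aT, and bF and bT are the same whether those are zero or not.

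**2. Illustration.** Inputs are assumptions, because the documents give none: standardised slopes bF = 0.6 and bT = 0.4, all residual SDs 1, c = 0, one change score per patient, 60 patients split 1:1, 3000 runs. By the formula, therapy through FM only (aF = 1, aT = 0) gives a total effect of 0.6 × 1 = 0.60. Therapy through trunk only (aF = 0, aT = 1.5) gives 0.4 × 1.5 = 0.60.

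| Truth | FM coefficient (rejected) | Trunk coefficient (rejected) | Adjusted treatment coefficient (rejected) | Unadjusted treatment effect |
|---|---|---|---|---|
| No therapy effect | 0.605 (99%) | 0.406 (84%) | 0.004 (4%) | −0.004 |
| Only through FM | 0.599 (99%) | 0.404 (83%) | 0.000 (5%) | 0.597 |
| Only through trunk | 0.596 (99%) | 0.402 (83%) | −0.006 (5%) | 0.592 |

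The first three results columns are what section 5.3 would report, and they do not distinguish the three cases. With 30 patients the pattern is the same at lower power: FM rejected in 81 to 83% of runs, trunk in 51 to 52%, treatment in 4 to 5%.

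**3. Which arm comparisons exist elsewhere.**

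| Measure | Arm comparison intended? |
|---|---|
| FM-arm | Yes: A1 question 1 concerns recovery of motor function; section 3.1 lists FM-arm among measures for comparing groups |
| Cortical activation | Yes, for CIMT: B1 question 1; section 5.2 sizes control and experimental groups |
| Wrist mechanics and reflexes | Yes: B3 questions 2 and 4; section 5.2 sizes each arm |
| Trunk movement | None stated: neither B2 question compares the arms |

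No stated analysis links an arm difference on any of these to the arm difference in ARAT.

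**4. Precision of the missing contrast.** Kinematics is listed with the additional Project B assessments (section 4.6), and section 4.5 takes 30 patients from each trial, so about 30/2 = 15 per arm. For an assumed difference of 0.6 SD, two-sided 5%, the noncentrality is 0.6 × √(15/2) = 1.64 on 28 degrees of freedom, giving power of about 35%. With 30 per arm it would be 0.6 × √(30/2) = 2.32, about 63%.

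**The case against.** The strongest reply is that the model does what Project C asks of it. Section 2.3 wants longitudinal relations between improvement and other changes, and section 5.3 describes its aim as an association. The Summary's promise rests on the whole programme, including the two randomised trials and Project B, and several arm comparisons on mechanism measures are already planned. All of this stands, and it confines the point to a gap between the programme question and the analyses stated for it. It does not close that gap, because compensation is carried by trunk movement and that is where no arm contrast is stated.

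A reader might infer three stronger things that the documents do not support.

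- *That the arms, or A1 and A2, are pooled in a strictly additive model.* This is a natural reading of treatment as one covariate, but the text does not say so or exclude an interaction, and a separate analysis plan could settle it. Fitting the model within each trial would leave both problems in place.
- *That the protocol will claim therapy-induced repair or compensation from the Wald P values, or read a null adjusted treatment term as no therapy effect.* No passage says this. The therapy effect comes from Project A. If treatment is among the bivariate regressions, its unadjusted coefficient would also be available, though no comparison of the two is planned and it would not separate the routes.
- *That the rejection rates near 100% are false-positive rates.* They are the power to detect slopes that the simulation itself made non-zero, and the protocol does not assign those tests the null that therapy does not act through the measure. Larger percentages can be had by assuming more. With a slope of 0.3 ARAT points per unit, a 6-point gain wholly through FM-arm needs 6/0.3 = 20 points on a 66-point scale.

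**Conclusion.** The point holds in limited form. The Summary and Introduction promise an answer about therapy-induced improvement. The section 5.3 model answers Project C's narrower question about improvement in general. Its FM-arm and trunk coefficients do not depend on whether therapy worked, and its treatment coefficient is not the total therapy effect. What is missing is an arm contrast on trunk movement and any stated link from arm differences in mechanism to the ARAT gain.

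The structural result follows from the algebra under a model without interaction. The percentages only illustrate it under assumed slopes. This is a fault in the support for a secondary, mechanistic claim and is cheap to mend. It is not an error in the trials' primary analyses.

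**What to change.** In section 5.3:

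1. Keep the change-on-change model and label it a description of recovery.
2. Add the randomised arm contrast on change in trunk bending and trunk rotation, beside that on FM-arm, within A1 and within A2.
3. State that the treatment coefficient adjusted for these change scores will not be read as the therapy effect.
4. Base any statement about therapy-induced restitution or compensation on the arm contrasts. Otherwise, replace the therapy-induced wording in the Summary and Introduction by improvements in general.

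Optionally, and as exploratory only, estimate the indirect effect through each route (arm effect on the measure times its slope on ARAT) with a bootstrap interval that resamples patients. State the assumption of no confounding between the measure and ARAT, which randomisation does not secure.

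The cost is wording and a small amount of analysis on data already planned, with no new patients or measurements. The drawback is precision: with about 15 patients per arm for trunk data in each trial, a non-significant contrast would not show that compensation is absent. Intervals should be reported and the claim kept modest.
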